### Randomization, allocation concealment, and blinding

2.3

All patients will be randomly allocated at a 1:1 ratio to either the VIT or TIE group by using a random number table generated by an independent statistical analyst with SPSS. In accordance with the 2025 WHO age classification, participants will be stratified into two age groups (40–65 years and 66–85 years) before randomization to ensure balanced distribution across intervention arms. The assignment details will then be sealed in opaque envelopes. After each participant provides written informed consent and completes their baseline assessments, the study coordinator will open the envelope to reveal the participant's group allocation.

Because of the nature of the intervention, neither the participants nor the instructors will be blinded; nevertheless, the outcome assessors and statistical analysts will remain blinded to group assignments.

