### Statistical analysis

2.7

Data analysis will follow the modified intention-to-treat principle to ensure complete randomization, minimize selection bias, and reflect real clinical practice. Missing data will be addressed using multiple imputation to reduce potential bias resulting from missing information, ensuring the robustness and accuracy of the analysis. All statistical tests will be performed according to a preestablished statistical analysis plan. SPSS (version 21.0) will be used for all data analyses, and two-tailed *p* < 0.05 will be considered to indicate statistical significance.

Continuous variables will be expressed as means ± standard deviations or median (Interquartile) where appropriate, and categorical variables as frequencies and percentages. Normality testing for continuous variables will be performed using the Shapiro–Wilk or Kolmogorov–Smirnov test, and homogeneity of variance will be assessed using the Levene test. For continuous variables that are normally distributed with equal variance, intergroup comparisons will be conducted using the independent-samples *t*-test. For continuous variables that do not meet the normality or homogeneity assumptions, the Mann–Whitney *U*-test will be employed. For discrete variables (such as the AE number and severity over 12 weeks), intergroup comparisons will be performed using the chi-square, Fisher exact, or Cochran–Mantel–Haensel χ^2^ test.

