### Sample size calculation

2.8

Our literature review indicated that the AE rate within 3 months after hospitalization for AECOPD is approximately 48.9% (5). Our preliminary data (unpublished) indicate that after VIT, the treatment failure rate at 90 days is approximately 15%. Therefore, the expected effect size between the two groups is about 33.9%. We set the significance level α = 0.05 and the statistical power at 80% (i.e., β = 0.20), with a dropout rate assumed to be 20%. The calculated values for *Z*_α_/2 and *Z*β are 1.96 and 0.84, respectively, with standard deviation σ = 0.614, effect size Δ = 0.339. Based on these parameters and sample size calculations, each group must include ≥32 patients. To ensure data accuracy and account for potential dropouts, we plan to recruit 40 patients per study group, totaling 80 participants.

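### Allocation is stratified by age group, but no listed test is tied to the age strata; the promised balance also depends on a within-stratum restriction that the article does not state

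*Protocol article*

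**What the plan says.** Section 2.3 allocates patients 1:1 "by using a random number table generated by an independent statistical analyst with SPSS". It adds that two age strata, 40–65 and 66–85 years, are formed "before randomization to ensure balanced distribution across intervention arms". It mentions no blocking, minimization or other restriction, and it does not say that the lists are unrestricted. Section 2.8 states that "we plan to recruit 40 patients per study group, totaling 80 participants".

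Section 2.7 covers the analysis. For continuous variables with normal distribution and equal variance, "intergroup comparisons will be conducted using the independent-samples" t-test; otherwise the Mann–Whitney test is used. For discrete variables, with AE number and severity as the examples, it offers chi-square, Fisher exact or CMH. It gives no rule for choosing among the three, no stratum for CMH, and no mention of age. It refers to a pre-established statistical analysis plan, which is not shown.

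**The concern.** Age is the one factor the sponsor singled out for balancing, yet nothing in Section 2.7 carries it into the comparison. When stratification works, it removes between-arm variation due to age. A test that ignores the strata still counts that variation in its standard error, so the interval is too wide and the test loses power if age is prognostic. The primary outcome, AE frequency, falls under the three-way choice, so whether age enters the main result is left open.

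A second question is whether the stated balance follows from the stated method. Strata deliver balance only when the sequence inside each one is restricted. Independent 1:1 draws within two strata have the same distribution as independent 1:1 draws overall.

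**Working it through.** **Inputs from the article.** Two age strata and 1:1 allocation (2.3); two-sided 0.05 (2.7); 80 patients, 40 per group, AE risk 48.9% under control and 15% under VIT (2.8).

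**Assumptions.** The article gives no stratum sizes and no AE risk by age. I take 40 patients per stratum, AE as a yes/no outcome (as Section 2.8 does), and control risks by age of 48.9%/48.9% (age not prognostic), 35%/63% or 25%/73%. The last two pairs average 49%.

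**The plan's own figures.** σ = √(0.489×0.511 + 0.15×0.85) = √0.3774 = 0.614, as stated. Then (0.614×2.80/0.339)² = 25.7, and 25.7/0.8 = 32.1, close to the stated "each group must include ≥32 patients". The calculation has no age term. This point disputes no figure in it.

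**Step 1: which listed tests use the age strata?**

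| Test in 2.7 | Uses age group? |
|---|---|
| t-test, Mann–Whitney | No |
| Chi-square, Fisher exact | No |
| CMH | It can, but no stratum is named and it is one of three options |

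**Step 2: cost of ignoring balanced strata (20 per arm in each).** Chi-square uses the variance p(1−p) at the pooled risk. The variance that applies under balanced strata is the mean of p(1−p) within strata.

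- 35%/63%: pooled 0.49×0.51 = 0.2499; within strata (0.2275 + 0.2331)/2 = 0.2303; ratio 0.922. The standard error is too large by 1/√0.922 = 1.04.
- 25%/73%: within strata (0.1875 + 0.1971)/2 = 0.1923; ratio 0.770. The standard error is too large by 1/√0.770 = 1.14.

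Exact enumeration of all 21⁴ outcomes (0 to 20 events in each of four cells), rejecting when |z| > 1.96 without continuity correction, gives:

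| Risks by age | Type I error, chi-square / CMH | Power, 25-point reduction in both strata | Power, risk ratio 0.15/0.489 = 0.307 in both strata |
|---|---|---|---|
| 48.9%/48.9% | 0.057 / 0.057 | 65.1% / 65.2% | 91.9% / 91.9% |
| 35%/63% | 0.047 / 0.050 | 65.6% / 68.6% | 92.4% / 93.1% |
| 25%/73% | 0.030 / 0.050 | 66.8% / 79.0% | 93.4% / 95.2% |

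For a 25-point reduction the loss is 3 to 12 points. In the last row that reduction takes the younger stratum to zero risk, so 12 points is an extreme case. At the plan's expected effect the loss is about 1 to 2 points.

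**Step 3: the same comparison under unrestricted allocation.** By simulation with risks from 48.9%/48.9% to 30%/60%, and 40 or 56 older patients, type I error is about 0.053–0.055 for chi-square and 0.049–0.050 for age-stratified CMH. Neither is seriously wrong.

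**Step 4: balance if, and only if, the lists are unrestricted.** With counts Binomial(n, 0.5):

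- One stratum of 40: P(arms differ by 6 or more) = 0.430. At least one of two strata: 1 − 0.570² = 0.675.
- All 80: P(exactly 40/40) = 0.089; P(35/45 or worse) = 0.314.
- Older-age share differing by 15 points or more between arms: about 21% of trials (22% counting exact ties). With 50 to 60 older patients it is about 13% to 18%.

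Permuted blocks of 4 and 6 within strata would hold the difference in each stratum to 3 at most.

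**The case against.** The strongest reply is that this is a condensed article. Block schemes are commonly left to the full protocol, and in a single-center trial with unblinded instructors there is good reason not to publish block sizes. A random number table names the source of randomness and does not rule out blocks. The 1:1 ratio and the exact 40 per group fit restricted lists well. That stands. A reader might infer that the lists are plain and that the stratification therefore has no effect, but the article does not say so. The figures in Step 4 are conditional and describe no stated procedure.

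A reader might also infer that the analysis ignores the strata altogether. That is too strong, because CMH is on the list for the outcome that matters most and can be stratified by age. It is also fair to say that the two halves pull apart: if allocation is in effect simple randomization, an unstratified test is valid (Step 3), and if stratification works, the balance complaint falls away. Ignoring the strata does not make the trial's inference invalid in either case.

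The choice of test and stratum may be settled in the statistical analysis plan. What survives is that Section 2.7 itself presents three tests as alternatives, four of its five named tests cannot use the strata, and the fifth is not linked to them.

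**Conclusion.** The point holds in a limited form. The design stratifies by age and no listed test is tied to that stratification. If the strata are balanced and age is prognostic, an unstratified chi-square test is conservative (type I error 0.047 or 0.030 rather than 0.050) and gives up about 3 to 12 points of power for a 25-point risk reduction, or about 1 to 2 points at the plan's expected effect. If age is not prognostic, the two analyses perform almost identically. These sizes rest on assumed stratum sizes and assumed AE risks by age; the article supports neither a particular age effect nor its absence.

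The balance point is secondary. The wording in Section 2.3 is justified only if the sequence is restricted within each age stratum, and the article leaves that open. It is a matter to confirm, not an error shown.

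**What to change.** In Section 2.7, replace the open choice among three tests with one pre-specified primary comparison of 12-week AEs that is stratified by or adjusted for age group. Examples are CMH with age group as the stratum, or a model with age group as a covariate. If the statistical analysis plan already fixes this, the article should say the same.

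In Section 2.3, state whether allocation is restricted within each age stratum, without giving block sizes. If the SPSS lists are unrestricted, generate them as permuted blocks of randomly varying size within each stratum, with sizes withheld from the study coordinator who opens the envelopes, or else drop the claim that balance is ensured.

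The cost is one model term or stratum, one list-generation setting and two sentences. No extra patients or staff are needed. The list can be changed only before allocation starts; the analysis should be fixed before anyone sees outcomes by group.

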### Interventions

2.4

All patients will receive two inhaler usage instruction sessions during hospitalization and will be followed up weekly via telephone over 12 weeks after discharge. Researchers blinded to the group assignments will implement this measure. It will ensure regular use of inhalation medications in both groups during the study period and enable recording of any possible AE events and their severity.

#### VIT group

2.4.1

VIT will be conducted based on the patient's inhaler type. The training will be performed on the basis of the Visualized Inhalation Technique Training System (OHM-50, ORANGER DTx, Tianjin, China), which our research team has codeveloped. This system provides simulated inhalation training with visualized PIFr and inhalation duration (hereinafter, “visualized training”) and simulated inhalation training using a medication-free canister equipped with a sensor (hereinafter, “sensor training”).

In visualized training, patients will observe real-time inspiratory flow curves during inhalation and compare them with a standard reference chart. The therapist will provide instruction based on patient performance until the patient achieves the required inspiratory flow rate over three consecutive attempts. Each training session will allow for ≤ 10 attempts per day.

Next, each patient will undergo sensor training, using a medication-free inhaler canister equipped with an inhalation sensor for simulation. This sensor can detect four types of errors:

E1: No inhalationE2: Hand-breath coordination issuesE3: Insufficient inhalation durationE4: Comprehensive error (i.e., at least two of the aforementioned errors)

The therapist will also instruct patients to perform a breath-hold maneuver after inhalation is completed. On the basis of the observed errors and sensor feedback, the therapist will provide targeted guidance. If necessary, they will demonstrate the accurate technique until the patient successfully completes three consecutive correct inhalation attempts. Each training session will allow for ≤ 10 attempts per day.

#### TIE group

2.4.2

TIE will follow the demonstration-based model recommended by the GOLD guidelines (20). A respiratory nurse will provide verbal instructions using an inhaler technique education template (Attachment 3) and demonstrate manual techniques, including empty canister operations, alongside the patient. The nurse will determine when to conclude the education session based on their judgment that the patient has performed three consecutive correct attempts. Each education session will allow for ≤ 10 attempts with the empty canister.

### Outcome measures

2.5

Table 1 outlines the items to be measured and the time window for data collection.

#### Primary outcome

2.5.1

The primary outcome of this study will be AE frequency within 12 weeks after discharge, which will be monitored weekly via telephone.

The GOLD 2024 guidelines define AECOPD as a sudden worsening of respiratory symptoms, with dyspnea as the primary symptom. Secondary symptoms may include increased sputum volume and thickness, aggravated coughing, and wheezing. During this study's weekly follow-ups, an AE will be recorded if the patient experiences a significant worsening of dyspnea (primary symptom) lasting for ≥2 days or if two or more secondary symptoms worsen beyond normal daily variation over ≥2 days. The duration of each exacerbation will be carefully documented to prevent record duplication during subsequent follow-ups. A structured interview and record form will be developed to capture data on the number of AECOPD exacerbations over 12 weeks after discharge. See Appendix 1 for additional details.

#### Secondary outcomes

2.5.2

The following secondary outcomes will be considered.

(1) EXACT-Pro scale score: The EXACT-Pro questionnaire allows patients to self-assess AE-related symptoms, including dyspnea, cough, sputum production, chest symptoms, and quality of life. The scale has good reliability and validity and consists of 14 items. Each item is scored from 0 to 5, with the total score being converted into a 0–100 scale based on logarithmic transformation. The higher the score, the greater the AE severity. We will collect the relevant data once daily over 12 weeks.

(2) AE severity: AE severity will be assessed according to the GOLD 2024 guidelines by using the following grading system: Mild, AE requiring short-acting bronchodilator treatment; Moderate, AE requiring short-acting bronchodilator plus antibiotics and/or oral corticosteroids treatment; and Severe, AE requiring hospitalization or emergency department visit. Based on these definitions and grading standards, a structured interview record form will be created to collect data on AE severity within 12 weeks after discharge. See Appendix 1 for additional details.

(3) All-cause mortality

(4) Inhalation technique assessment: This will be divided into inhalation flow rate evaluation and inhalation operation checklist.

(a) Inhalation flow rate evaluation: This will be performed using a portable pressure-flow measurement device (OHM-50; ORANGER DTx, Tianjin, China). While seated, the patient will use a special mouthpiece identical to the one in their regular inhalation device, as selected by the evaluator. The patient will be instructed to inhale as they normally would when taking their medication. The test will be repeated three times, and the best result will be recorded for further analysis. This evaluation will include three objective measures: PIFr, effective inspiratory time (EIT), effective inspiratory volume, and integrated inspiratory flow system (IIFS) score (IIFSs). EIT is the duration over which the inspiratory flow rate remains within the correct range during the PIFr test. EIV, representing the inhaled volume during the EIT, is determined by calculating the area under the inspiratory flow curve within the EIT. IIFS is a standardized scoring system based on objective data. IIFSs, calculated by comparing the measured inspiratory parameters with a standardized model, is a percentile-based score on a 100-point scale, reflecting the overall effectiveness of the patient's inhalation performance.

(b) Inhalation operation checklist: This will require the use of a medication-free inhaler canister equipped with an inhalation sensor for simulation. The patient will be asked to perform three simulated inhalations. The evaluator will observe the patient's inhalation steps and then record the results on the checklist by using the sensor's feedback. See Attachment 2 for the significance of the sensor feedback and the inhalation operation checklist. The entire process will be video recorded for future reference and review.

(5) Lung function: This will be assessed through spirometry using automated equipment as indicated in the guidelines.

(6) Physical fitness:

(a) 6-Min walk test: This test will be performed according to the recommendations of the European Respiratory Society/American Thoracic Society (21).

(b) Grip strength: This will be assessed bilaterally using a dynamometer (Jamar Plus+ Digital Hand Dynamometer, Fabrication Enterprises Inc, USA).

(c) Maximum voluntary contraction of knee extension: This will be measured using a handheld dynamometer (MicroFET 2; Hoggan, West Jordan, UT, USA).

(d) Respiratory muscle function: This will be assessed based on maximal inspiratory and expiratory pressures by using a Gio Digital Pressure Gauge (22).

(7) Chronic activity-related dyspnea: This will be assessed using the modified Medical Research Council dyspnea scale.

(8) Inhaler medication adherence: The Chinese version of the Test of Adherence to Inhalers (TAI) will be used to assess treatment adherence. TAI scores, ranging from 10 to 50, are used to categorize adherence into three levels: low (≤45), moderate (46–49), and high (50). This scale has good reliability and validity (23).

(9) Health-related quality of life: This will be measured using the COPD Assessment Test.

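### AEs are counted on symptoms but graded only by treatment, so an untreated AE has no severity grade; the unit for the severity test is also not named

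*Protocol article*

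**What the plan says.** Section 2.5.1 (Primary outcome) states that "an AE will be recorded if the patient experiences a significant worsening of dyspnea" for at least two days, or if two or more secondary symptoms worsen for that long. No treatment is needed. Episode durations are recorded so that one AE is not counted twice, which means that a patient can contribute several AEs.

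Section 2.5.2, item (2), grades severity by care required: "Mild, AE requiring short-acting bronchodilator treatment; Moderate, AE requiring short-acting bronchodilator plus antibiotics and/or oral corticosteroids treatment". The third grade, severe, needs hospitalization or an emergency department visit. The record form is to be built on these definitions, and further detail is left to Appendix 1, which is not shown.

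Section 2.7 (Statistical analysis) states: "For discrete variables (such as the AE number and severity over 12 weeks), intergroup comparisons will be performed using the chi-square". The sentence goes on to list Fisher exact and Cochran–Mantel–Haenszel (CMH) tests as alternatives. It does not name the unit of analysis for severity.

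**The concern.** There are two separate problems.

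First, the rule that creates an AE and the rule that grades it use different criteria. Some AEs can enter the primary outcome and then have nowhere to go in the severity outcome. Weekly telephone questioning about symptoms makes untreated AEs plausible. If they are dropped, called mild or treated as missing case by case, the severity comparison depends on an unstated choice.

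Second, severity is an ordered grade attached to each AE, while the listed tests, as usually applied, need independent observations. Nothing shown says how several AEs in one patient become one value, or where AE-free patients are placed. If events were tabulated, two things would follow: correlated grades within a patient would raise the false-positive rate, and the comparison would be limited to patients selected by having had an AE after randomization. Ordinary chi-square and Fisher tests also ignore the order of the grades.

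The abstract's background gives reducing both AE frequency and severity as the aim, so this secondary outcome carries some weight.

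**Working it through.** **Grading gap.** No arithmetic applies, so the two definitions are set side by side.

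- Entry as an AE (2.5.1): symptoms worse for at least two days; treatment irrelevant.
- Mild (2.5.2): requires a short-acting bronchodilator.
- Moderate: requires a short-acting bronchodilator plus antibiotics and/or oral corticosteroids.
- Severe: requires hospitalization or an emergency visit.

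An AE with none of this care meets the first line and none of the others. As worded, an AE managed with antibiotics or oral corticosteroids but no short-acting bronchodilator, and no hospital contact, is also ungraded. The documents give no figure for how often either occurs.

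**The plan's own figure.** The plan gives no number for severity, only the sample size (2.8). Inputs: "the AE rate within 3 months after hospitalization for AECOPD is approximately 48.9" percent; for VIT, "the treatment failure rate at 90 days is approximately 15" percent; z-values 1.96 and 0.84; σ = 0.614; Δ = 0.339.

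- σ = √(0.489 × 0.511 + 0.15 × 0.85) = √0.3774 = 0.614, already the sum of both arms' variances.
- n = (0.614 × 2.80 / 0.339)² = 25.7 per group.
- With 20% dropout: 25.7 / 0.8 = 32.1, matching the stated 32. Then 32 / 0.8 = 40, the recruitment target.

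The figure reproduces and does not bear on severity. It supplies the 32 per arm used below, which is also what remains of 40 after 20% dropout.

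**Who is left in an events-only table**, 32 per arm:

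- TIE: 32 × 0.489 = 15.6, about 16 patients with an AE; about 16 AE-free.
- VIT: 32 × 0.15 = 4.8, about 5 patients with an AE; about 27 AE-free.

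**Type I error if events were tabulated.** 3,000 simulated null trials per setting, 32 per arm, Pearson chi-square at the protocol's two-sided 5% level. Assumptions not in the documents: grade mix 40/35/25%; Poisson or negative binomial counts (dispersion 1); latent within-patient severity correlation 0 to 0.9. The chance of at least one AE is the same in both arms: 48.9%, or 32%, which is (48.9 + 15)/2. Rejection rates for the event-level test:

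| Chance of any AE, count model | Events per trial | Corr. 0 | 0.3 | 0.6 | 0.9 |
|---|---|---|---|---|---|
| 32%, Poisson | about 25 | 5.0% | 5.9% | 6.3% | 8.5% |
| 32%, neg. binomial | about 30 | 4.5% | 6.6% | 10.0% | 14.3% |
| 48.9%, Poisson | about 43 | 4.9% | 7.0% | 7.7% | 12.3% |
| 48.9%, neg. binomial | about 61 | 5.5% | 10.1% | 15.3% | 23.8% |

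Monte Carlo standard error near 5% is √(0.05 × 0.95 / 3000) = 0.4 percentage points. A patient-level chi-square on worst grade, with a no-AE category, rejects 3.8–5.5% across all sixteen settings.

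**Direction of the selection effect.** As a limiting case with the assumed 40/35/25 mix: if VIT removed every mild AE and no other, the severe share among remaining VIT events would rise from 25% to 25/60 = 42%, although no patient was worse off. This shows the mechanism; it is not an estimate.

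**The case against.** The strongest objection is that section 2.7 does not commit to an event-level test. It names AE number and severity together. AE number is naturally one value per patient, so severity may be meant the same way. Grading each AE is data collection and does not fix the unit of analysis. A reader might infer that the trial will test events as if they were independent patients and will leave out AE-free patients. The documents say neither, and a worst-grade-per-patient table fits section 2.7 equally well. Both consequences must stay conditional.

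Nor does the abstract settle the unit. Where it speaks of the severity of each AE, it adds the EXACT-Pro score in parentheses. That is a separate outcome from the treatment-based grade.

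A reader might also quote the 24% error rate as the size of the problem. It needs a within-patient correlation of 0.9 together with overdispersed counts, and at zero correlation there is no inflation.

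The unit of analysis is commonly settled in the analysis plan, which section 2.7 mentions and which is not shown. That stands against treating the missing unit alone as an error. It does not remove the misfit between a grade given to each AE and tests that need independent observations. CMH is indeed on the list, so part of the remedy is already allowed for, but CMH does not by itself repair clustering of events within patients.

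Appendix 1 might add a category for untreated AEs. But the record form is said to follow the stated definitions, so the mismatch remains in the text as published.

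**Conclusion.** The grading gap holds on the text: sections 2.5.1 and 2.5.2 do not match, and some AEs that count in the primary outcome have no severity grade. Its frequency cannot be derived from the documents.

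The testing point holds conditionally. If the severity table counts events, type I error is roughly 6–15% at nominal 5% for within-patient correlations of 0.3 to 0.6, and the comparison rests on about 16 against 5 patients. The error rates depend on the assumed grade mix, dispersion and correlation; the patient counts depend on the protocol's planning rates. If the table has one row per patient, neither problem arises. Either way, an unordered test makes poor use of an ordered outcome. Because this is a secondary outcome, the point should be settled before unblinding but does not threaten the primary analysis.

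**What to change.** Reconcile sections 2.5.1 and 2.5.2 so that every recorded AE has a place in the severity outcome, including the combinations of care that fit no grade as worded.

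For analysis, give each randomized patient one ordered value, the worst over 12 weeks: no AE; AE without any listed treatment; mild; moderate; severe. Compare arms with an ordinal (row-mean-score) CMH test stratified by the age group used in randomization (section 2.3), or with a proportional-odds model adjusted for that stratum. This keeps all randomized patients, removes the clustering, and uses the order of the grades. A moderate-or-severe AE rate can be added as an optional supportive analysis.

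The cost is analysis-plan wording and one extra category on the record form. The downside is that worst grade ignores the number of events, but the primary outcome already covers that.
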